### 2.2. Criteria for Feasibility and Acceptability

Feasibility will be defined quantitatively by examining the **recruitment rate** (i.e., the proportion of eligible patients who consent to participate) and the **retention rate** (i.e., the proportion of enrolled patients who complete scheduled follow-up assessments over the 12-month period). In the absence of literature benchmarks and prior pilot data, a pragmatic threshold *of 80% recruitment rate* of eligible patients will be set as a measure of feasibility.

Acceptability will be operationalized as an *overall retention rate of 50% or more of the recruited patients* over 12 months. In addition, this study will look at feasibility and acceptability by follow-up modality, comparing the recruitment and attrition rates between face-to-face assessments at the main hospital and remote assessments at the other hospitals. A significantly lower recruitment rate or higher attrition rate in the remote modality, as compared to the face-to-face approach, will be interpreted as indicative of reduced feasibility and acceptability.

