### 2.4. Statistical Methods

Baseline characteristics will be reported as means ± SD, or medians [IQR] for continuous variables, and as frequencies (%) for categorical variables. Prevalence of psychological distress, cognitive impairment, fatigue, symptoms of post-traumatic stress, and reduced quality of life will be estimated at all timepoints; exact 95% confidence intervals will be calculated. Reduced quality of life will be defined as an EQ-5D-5L VAS score at least 7 points lower than the age-matched Italian general population mean [26], based on established minimal clinically important differences identified in chronic disease populations [27,28].

Incidence rates (expressed per 100 person-years) for mood disorders, post-traumatic stress symptoms, reduced quality of life, and cognitive impairment will be calculated for participants free of the respective condition at baseline. Incident cases will be defined as follows: a HADS subscale score > 8 for mood disorders (either anxiety or depression subscale), IES-R ≥ 33 for post-traumatic stress symptoms, a MoCA score < 26 for cognitive impairment, and a decrease of ≥7 points from the age-matched normative mean on the EQ-5D-5L VAS for reduced quality of life. Baseline status will be determined using the initial T0 assessment; if T0 data are missing, the T1 (1-month) assessment will be used. Participants with missing data at both T0 and T1 for a given outcome will be excluded from the incidence rate calculation for that outcome. Incidence rates will be reported with exact 95% confidence intervals.

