Longitudinal changes in HADS, MoCA, EQ-5D-5L, and IES-R from T0 to T4, as well as differences in the retention rate between patients seen remotely or face-to-face, will be analyzed using mixed-effects models (linear or logistic) incorporating time and potential covariates (e.g., age, sex, comorbidities). Models will initially include random intercepts and slopes at participant and hospital levels. Different residual covariance structures (e.g., first-order autoregressive [AR(1)]) will also be explored. Model selection will be guided by the Akaike Information Criterion (AIC) and Bayesian Information Criterion (BIC); simpler random intercept-only models will be adopted if convergence issues arise. Missing data will be handled using Multiple Imputation by Chained Equations (MICE), assuming a Missing At Random (MAR) mechanism. Twenty imputed datasets will be generated, incorporating all key predictors and outcomes, as well as hospital ID. Participants who completely withdraw from this study will be treated as censored at their last observation without further imputation. Sensitivity analyses comparing complete-case and imputed datasets will be conducted to assess the robustness of the findings. A *p*-value < 0.05 (two-sided) will denote statistical significance.

Qualitative data will be derived from detailed notes taken during semi-structured interviews; the analysis will employ a framework approach, well-suited for applied qualitative research with pre-defined areas of inquiry [29]. The analytic process will involve familiarization with the notes, followed by the development of a thematic framework based on the predetermined domains. Data will then be indexed using both deductive codes—stemming from the interview guide—and emergent codes that may arise from the content of the notes. A matrix will be constructed to chart responses across cases, enabling systematic cross-case comparisons.

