## 4. Discussion

Survivors of OHCA face a broad array of challenges, extending beyond the immediate physical aftermath to include psychological distress, cognitive impairments, and chronic fatigue. Depression is notably associated with higher mortality in this population [31]. Despite increased awareness, however, few structured pathways exist to identify and address these non-physical sequelae. Current pathways involve follow-ups being completed mostly or entirely in person, by the hospital that admitted the patients following their OHCA [12,14]; despite this approach having clear advantages (namely, full access to the clinical history of the patient; patient being already familiar with the hospital/treating team; face-to-face meeting being more accessible to some patients, etc.), it also requires more resources in terms of personnel, training required and clinic space.

The prospective, multicentric REVIVE project aims to investigate the feasibility and acceptability of a centralized, sub-regional system to investigate mood, cognition, fatigue, psychological wellbeing, and overall quality of life at multiple time points up to 12 months post-discharge. It also aims to be the first study to systematically assess psychological distress, cognitive status, and quality of life in a sizable Italian cohort of OHCA survivors.

Study limitations may include attrition (e.g., among patients with cognitive deficits or significant psychological difficulties) and the non-randomized nature of the intervention. Remote/telemedicine follow-up options will aim to reduce dropout; however, they might also constitute a barrier for some patients who feel less comfortable using new technology.

Should the REVIVE study demonstrate the need for a tailored psychological approach and that our approach is feasible and welcomed by the patients, it could serve as a guide to build up similar and permanent programs to help patients thrive and not simply survive after a cardiac arrest.

The results are expected to guide future recommendations on the delivery of follow-up/assessment services and help establish new standards of post-resuscitation care.

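### Complete withdrawals are left out of the imputation, so later-visit prevalences are neither corrected nor tested for informative withdrawal

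*Protocol article*

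**What the plan says.** All of the analysis rules are in section 2.4 of the protocol article.

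- Target: "Prevalence of psychological distress, cognitive impairment, fatigue, symptoms of post-traumatic stress, and reduced quality of life will be estimated at all timepoints", and "exact 95% confidence intervals will be calculated".
- General rule: "Missing data will be handled using Multiple Imputation by Chained Equations (MICE), assuming a Missing At Random (MAR) mechanism". Twenty datasets are planned, with hospital among the variables in the imputation model.
- Exception: "Participants who completely withdraw from this study will be treated as censored at their last observation without further imputation".
- Robustness: "Sensitivity analyses comparing complete-case and imputed datasets will be conducted to assess the robustness of the findings".

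Three other places bear on the point. Section 2.2 counts follow-up as acceptable with an "overall retention rate of 50% or more of the recruited patients". Section 4 concedes: "Study limitations may include attrition (e.g., among patients with cognitive deficits or significant psychological difficulties". Section 3.1 describes barriers to remote follow-up as predictable, particularly in older patients and those with neurocognitive or psychological problems.

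**The concern.** The prevalence at 6 or 12 months is a cross-sectional proportion. Someone who withdrew at 2 months has no status at either visit, and calling that person censored does not create one. Without imputation, the person drops out of the proportion. The later-visit prevalences then describe participants who have not withdrawn, although the plan says missing data are handled under MAR. MAR is only useful here if earlier scores are allowed to inform the missing later ones, and the exception blocks that for this group.

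The robustness check has the same gap. The complete-case set has no post-withdrawal values, nor do the imputed sets, and neither departs from MAR. Agreement between them would say nothing about whether the people who withdrew were worse off, yet it would be reported as robustness.

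Prevalence is one of the two stated aims. The patients whom sections 3.1 and 4 name as at risk of loss have the conditions being counted. If they do withdraw more often, prevalence is understated and the exact interval gives no sign of it.

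**Working it through.** **1. The plan's own precision figure.** Section 3.2 gives 350 eligible × 0.80 consenting = 280, a prevalence of 25%, and 5% precision with 95% confidence at 6 months. The formula is n = 1.96² × p(1 − p) / d². With p = 0.25 and d = 0.05, n = 3.8416 × 0.1875 / 0.0025 = 288.1. At n = 280 the half-width is 1.96 × √(0.1875 / 280) = 5.07 points, which rounds to the stated 5. The claim reproduces approximately, provided that all 280 contribute at 6 months.

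**2. Bias from leaving withdrawals out.** Let w be the share completely withdrawn, p_s the prevalence in the others, p_w the prevalence in those withdrawn, and OR the odds ratio between the two groups. Solve

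(1 − w) p_s + w p_w = 0.25, with p_w / (1 − p_w) = OR × p_s / (1 − p_s).

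The plan estimates p_s if imputation fully recovers every other missing value, which is a favourable assumption. The bias is p_s − 0.25. The article gives neither w nor OR, so both are assumed. The 25% is the planning value from section 3.2.

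| Withdrawn | OR 1.5 | OR 2 | OR 3 |
|---|---|---|---|
| 15% | 23.8% (-1.2) | 22.8% (-2.2) | 21.5% (-3.5) |
| 25% | 23.0% (-2.0) | 21.5% (-3.5) | 19.4% (-5.6) |
| 30% | 22.6% (-2.4) | 20.9% (-4.1) | 18.4% (-6.6) |
| 50% | 21.2% (-3.8) | 18.6% (-6.4) | 15.1% (-9.9) |

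Check of one cell (25%, OR 2): p_s = 0.2153 has odds 0.2744. Doubled, that is 0.5488, so p_w = 0.3543. Then 0.75 × 0.2153 + 0.25 × 0.3543 = 0.250.

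The 50% row is the worst case. It treats all of the non-retention that section 2.2 tolerates as complete withdrawal.

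**3. What imputation and the planned comparison can and cannot do.** A simulation used 50% retention, a correlation of 0.6 between earlier and later score, 70% of the missing patients being withdrawals, and a true prevalence of 24.9%. All of these are assumptions. Each cell gives the results for a weaker and a stronger dependence of dropout on the score.

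| Dropout depends on | Complete-case | Plan as written | Everyone imputed |
|---|---|---|---|
| Earlier observed score (MAR) | 20.3%, 17.0% | 22.5%, 20.7% | 25.0%, 25.0% |
| Current unobserved score (MNAR) | 17.5%, 11.4% | 18.6%, 13.0% | 19.8%, 14.8% |

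Under MAR, the exception alone costs 25.0 − 22.5 = 2.5 to 25.0 − 20.7 = 4.3 points, and imputing everyone removes that bias. Under MNAR, the planned comparison shows differences of only 18.6 − 17.5 = 1.1 and 13.0 − 11.4 = 1.6 points, while the plan's estimate is off by 24.9 − 18.6 = 6.3 and 24.9 − 13.0 = 11.9 points. Imputing everyone under MAR does not repair this case, so a separate MNAR analysis is needed.

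**The case against.** Much can be said for the plan, and several stronger readings fail.

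- *A reader might infer that the plan is complete-case throughout, or that withdrawal is the main source of missing data.* The article gives no split between withdrawal, missed visits and loss of contact. The exception covers only complete withdrawal, and everyone else is imputed. The complete-case comparison can therefore show some bias arising from non-attenders who did not withdraw.
- *A reader might infer that withdrawn patients' scores are discarded.* They are not. They count in the prevalence at visits attended, in person-time, and in the mixed models, which under likelihood estimation use them under MAR. Only the later-visit prevalences forgo them.
- *A reader might take 50% as the expected loss.* It is a floor for acceptability over 12 months, whereas the precision claim is for 6 months. With 15% withdrawn, every bias in the table is smaller than 5 points.
- *A reader might say that the protocol expects loss of affected patients.* Section 4 says only that this may occur, and offers remote follow-up as mitigation. A downward bias is plausible but not established.
- *A reader might add the baseline rule for incidence, "if T0 data are missing, the T1 (1-month) assessment will be used".* That is a separate matter from withdrawal. A case at T1 whose T0 was done is incident only if T0 was negative.

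It is also fair that a condensed article may leave MNAR analyses and pooling details to a fuller document. That does not answer the core of the point, which is a rule that the article states, not one that it omits. None of these objections gives withdrawn patients a place in the 6- and 12-month prevalences.

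**Conclusion.** The point holds for prevalence at visits after withdrawal. The no-imputation rule takes withdrawn participants out of those estimates and gives up a correction that the announced MAR imputation could make. The named sensitivity comparison cannot reveal informative withdrawal. T0 prevalence and the recruitment and retention criteria are not affected, and for the person-year incidence rates censoring is ordinary practice.

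The size depends on two quantities that the documents do not give: how many withdraw completely, and how much likelier those patients are to be cases. For 15% to 30% withdrawn and odds ratios of 1.5 to 3, the bias runs from -1.2 to -6.6 points. The worst case of 50% reaches -9.9. Against a stated precision of 5 points, that ranges from minor to larger than the planned margin. The figures are illustrations, not forecasts.

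**What to change.** 1. Limit the censoring sentence in section 2.4 to the incidence rates.
2. For prevalence at T1 to T4, include withdrawn participants who are alive in the MICE model, using their earlier scores, age, sex, assessment mode and hospital. Do this where consent allows use of data already collected, and impute nothing after death.
3. Pool the prevalences by Rubin's rules, because an exact binomial interval does not carry the imputation variance.
4. Keep the complete-case comparison and add a delta-adjusted (MNAR) analysis of the later-visit prevalences, for example multiplying the odds of being a case in those withdrawn by 1, 1.5, 2 and 3.

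The cost is a change of wording, some programming, and wider intervals at the later visits. No new data are required. The change should be made before outcome data are examined.

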## 3. Expected Results

### 3.1. Investigation of the Feasibility and Acceptability of a Sub-Regional “Hub and Spoke” Model of Post-Discharge Care Delivery

There is growing evidence that management of OHCA in “cardiac arrest centres”, and regionalization of post-cardiac arrest care may be beneficial to improve outcomes ranging from survival to long-term functional abilities (see [30] for a review)—even though there is still no definitive evidence in this area. The feasibility and acceptability of providing post-discharge follow-up care in a centralized manner at a regional/sub-regional level, however, are still unexplored.

Potential benefits of this approach revolve around leveraging the infrastructure, resources, personnel, and experience of a leading high-volume “cardiac arrest centre” to provide high-quality post-OHCA care in line with international guidelines; predictable barriers, however, could be encountered in the acceptability of this service when provided remotely, especially for older people and for those with neurocognitive impairments and/or psychological difficulties. It is expected that REVIVE will help to provide novel evidence in this area to inform the development of new guidelines.

### 3.2. Identification of Prevalence of Mood Disorders in OHCA Survivors

Based on Lombardia CARe figures, approximately 5200 OHCAs occur yearly in the regional area, and, in about 3500 of them, resuscitation is attempted. Of these, about 600 survive to hospital admission, and about 175 per year are discharged alive with CPC 1–2 or mRS ≤ 3. Therefore, over 24 months, about 350 eligible survivors are expected. Assuming 80% of them consent to be included in this study (about 280), this cohort will be sufficient to identify the presence of symptoms of at least mild anxiety or depression in 25% of cardiac arrest survivors at 6 months from the event, with 5% precision and 95% confidence (Appendix A, Table A2). Although the prevalence of mood disorders after OHCA has been investigated by several studies, REVIVE will be the first one to do so at the sub-regional level in Italy.

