## Abstract

**Background/Objectives**: Most survivors of out-of-hospital cardiac arrest (OHCA) may suffer from cognitive, mental difficulties, and fatigue, which negatively impact their quality of life, despite a good physical recovery. However, no definitive data are available on this topic, so this study aims to assess the feasibility and acceptability of a centralized, sub-regional screening system for OHCA survivors in Italy and the prevalence of these disorders. **Methods**: OHCA survivors discharged with good neurological outcomes (Cerebral Performance Category (CPC) ≤ 2 and modified Ranking Scale (mRS) ≤ 3) from hospitals in the “Lombardia CARe” registry will be evaluated by a clinical psychologist using the Montreal Cognitive Assessment (MoCA), Hospital Anxiety and Depression Scale (HADS), EQ-5D-5L for quality of life, and the Impact of Event Scale-Revised (IES-R) at pre-discharge or within 15 days and then at 1, 3, 6, and 12 months. Patients with clinical issues will be referred for psychological support or to a community rehabilitation program. Feasibility will be defined as a recruitment rate ≥ 80% and acceptability as a retention rate ≥ 50% over 12 months. **Results**: Based on historical data from the Lombardia CARe, an estimated 350 eligible survivors are expected, which will allow estimation of a prevalence ranging between 20% and 30% with 5% precision and 95% confidence. **Conclusions**: This study will be the first in Italy to evaluate the feasibility and acceptability of a centralized, sub-regional system for pre-/post-discharge evaluation of cognitive impairment, mental health, and quality of life in a large cohort of OHCA survivors, documenting the prevalence of these disorders.

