#### 2.1.1. Inclusion Criteria

Patient must be ≥18 years and have survived an OHCA with attempted resuscitation by the Emergency Medical System. They display a **CPC 1–2 or mRS ≤ 3** at discharge and are capable of providing written informed consent.

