#### 2.1.2. Exclusion Criteria

Patients unable to speak the language to a sufficient degree to be able to participate in the assessments will not be recruited. In addition, patients with acute, currently unresolved psychological disorders of moderate/severe intensity—e.g., major depression, schizophrenia—will not be recruited in this trial.

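### The 350 'eligible survivors' and about 280 enrolled are upper bounds: consent capacity, language and psychological-disorder criteria are not deducted, and the 5% precision has no margin to absorb them

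*Protocol article*

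**What the plan says.** Section 3.2 of the protocol article starts from about 5200 cardiac arrests a year. It narrows these to about 3500 with attempted resuscitation and about 600 admitted alive, and then states: "about 175 per year are discharged alive with CPC 1–2 or mRS ≤ 3. Therefore, over 24 months, about 350 eligible survivors are expected". The Abstract repeats the label: "an estimated 350 eligible survivors are expected".

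The only later reduction is for consent: "Assuming 80% of them consent to be included in this study (about 280"). Section 3.2 says that this cohort suffices to find "symptoms of at least mild anxiety or depression in 25% of cardiac arrest survivors at 6 months from the event", with a precision of 5 points at 95% confidence, and refers to Table A2.

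Eligibility itself is set elsewhere and is narrower. Section 2.1.1 asks that patients meet the CPC or mRS condition "at discharge and are capable of providing written informed consent". Section 2.1.2 adds two exclusions. One is language: "Patients unable to speak the language to a sufficient degree to be able to participate in the assessments will not be recruited". The other is an acute, still unresolved psychological disorder of moderate or severe degree. Section 2.2 defines the recruitment rate as consenting patients over eligible patients.

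**The concern.** The word 'eligible' in section 3.2 and the Abstract is attached to a count that has not passed all of the eligibility criteria. Three conditions are missing from the chain: capacity to consent, sufficient language, and absence of an acute unresolved psychological disorder. Consent cannot stand in for them, since by section 2.2 it is measured only after eligibility is settled. Ineligibility on these grounds is therefore deducted nowhere.

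At stake are the stated cohort size and the precision claim built on it. The study could reach exactly 80% recruitment among eligible patients and still enrol fewer than 280. Since 280 is already at the edge of what the precision claim needs, any such loss widens the interval beyond the stated 5 points.

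**Working it through.** **Inputs.** From section 3.2: 175 good-outcome survivors per year, 24 months, 80% consent, 25% prevalence at 6 months, 5-point half-width, 95% confidence. No document gives a share failing the criteria of sections 2.1.1 and 2.1.2 that are missing from the chain. Call that share *e*.

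**Step 1: reproduce the plan's counts.**
- 175 × 2 = 350
- 350 × 0.80 = 280

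Both are exact, so the plan's figures correspond to *e* = 0.

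**Step 2: reproduce the precision basis.** Table A2 follows n = 1.96² × p(1 − p) / d². At d = 0.05 this gives 255 for p = 0.21, 329 for p = 0.31 and 384 for p = 0.51, as tabulated. For the case in section 3.2:
- n = 1.96² × 0.25 × 0.75 / 0.05² = 288.1
- half-width at n = 280: 1.96 × √(0.25 × 0.75 / 280) = 5.07 points

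So 280 agrees with the claim to rounding, but from just below. At 80% consent, 288.1 enrolled would need 288.1 / 0.80 = about 360 eligible patients, which is more than 350. There is no slack even at *e* = 0.

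**Step 3: let some of the 350 be ineligible.** Eligible = 350 × (1 − *e*); enrolled = 0.80 × eligible; half-width = 1.96 × √(0.1875 / enrolled). The values of *e* are assumptions for illustration.

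| Assumed *e* | Eligible | Enrolled at 80% | Half-width at 25% (points) |
|---|---|---|---|
| 0% (plan) | 350 | 280 | 5.07 |
| 5% | 332.5 | 266 | 5.20 |
| 10% | 315 | 252 | 5.35 |
| 20% | 280 | 224 | 5.67 |

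These half-widths assume that every enrolled patient is assessed at 6 months. Loss to follow-up is a separate matter and is not included.

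**Step 4: the direction.** Enrolled equals 280 only if no survivor with a good neurological outcome fails any of the three criteria. For any *e* above zero it is lower. The direction therefore follows from the text; the size does not.

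**The case against.** The strongest reply is that nothing is miscalculated. Both products are exact, the figures are given as approximate throughout, and a condensed article on an observational study may leave a screen-failure allowance to the full protocol. Capacity to consent may also overlap heavily with a good neurological outcome, so the further loss could be small. At 5% to 10% ineligible the half-width grows by only about 0.1 to 0.3 points.

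Much of this stands. It is not an arithmetic error, and the effect may be modest. But the article does more than omit an allowance: it presents 350 as following from the registry count and calls those patients eligible, against its own criteria. Nor is zero exclusion a safe default. The Introduction reports at least moderate depressive symptoms in more than a third of good-outcome patients in the pilot. That is not an exclusion rate, since symptoms are not a diagnosis and the timing may differ, but it makes the psychological criterion hard to treat as empty.

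Four stronger readings are tempting, and the documents do not support them:
- **That minors are counted in the 350.** Section 3.2 does not say whether the registry figure is limited to adults, and silence does not show that the age limit is unapplied.
- **That only the neurological criterion was applied.** Attempted resuscitation and survival to discharge are also in the chain, and both belong to the inclusion criteria.
- **That 350 is the number to be screened.** Section 2.1.3 has the team monitoring all registry admissions daily, so screening starts upstream of this count.
- **That protocol exclusions would be read as poor recruitment.** Section 2.2 already uses eligible patients as the denominator, and no section makes 350 an accrual benchmark.

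**Conclusion.** The point holds as one about stated planning figures. The 350 eligible and about 280 enrolled are best-case values under the protocol's own criteria, and the 5-point precision at 25% prevalence rests on them with no margin (about 288 needed; 280 gives 5.07 points).

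How far the true figures fall short cannot be derived from the documents. The illustrative range of 5% to 20% ineligible, which is an assumption, gives 266 to 224 enrolled and half-widths of 5.2 to 5.7 points. The loss of precision is small at the lower end and still below one point at the upper end. The feasibility criterion and its 80% threshold are unaffected, because they are already defined on eligible patients.

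**What to change.** In the Abstract and section 3.2, describe 350 as the expected number of survivors discharged with good neurological outcome before the remaining eligibility criteria are applied. Add one step for the share expected to meet those criteria, taken from registry data if available, or otherwise given as a range labelled as an assumption. Apply the 80% consent rate to the result, and restate expected enrolment and the precision it gives. Section 2.2 needs no change.

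The cost is a rewording and one more line of calculation, with slightly less favourable enrolment and precision figures. No patients, visits or procedures are added.
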